**For Dukes' B3 and C patients only:**

- Rev. 9/97, 8/99
- 3.28 Have WBC  $\geq 3000/\text{mm}^3$  and platelets  $\geq 100,000/\text{mm}^3$ ,  $\leq 1$  week prior to beginning adjuvant 5-FU/leucovorin therapy.
- 3.29 Have adequate renal (serum creatinine  $\leq 2.0$ ) and hepatic function (bilirubin  $\leq 2.0$ ), within one week prior to beginning chemotherapy.

- Rev. 9/95, 9/97
- 3.3 Eligibility Criteria for Re-Registration (for patients randomized post-operatively)
- All Dukes' B2, B3, and C patients must be re-registered  $\leq 35$  days post-op, after histopathological confirmation of tumor and Dukes' staging classification. Dukes' A, B1, and D patients will be removed from the study and will be treated at the discretion of their physician. Survival data will continue to be collected on Dukes' A, B1, and D patients until death.

Dukes' B2 patients will have perioperative 5-FU **continued** to completion, if so assigned, but will receive NO further adjuvant treatment. At the time of re-registration, Dukes' B2 patients will be followed on observation until relapse or death.

- Rev. 9/97
- Patients with Dukes' B3 and C disease must begin adjuvant 5-FU/leucovorin treatment between 21 and 35 days following surgery.

- 3.31 Must have pathologic classification of Dukes' B2, B3, or C disease (see Appendix IV for classification details) by the contributing institution.
- 3.32 Patient must be re-registered  $\leq 35$  days after surgery.
- 3.33 Have ECOG Performance Status of 0, 1 or 2.
- 3.34 Started perioperative 5-FU, if assigned, within 24 hours of surgery.

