### 2.0 **OBJECTIVES**

Rev. 9/97 2.1 To determine if adjuvant therapy with one week of continuous 5-FU given within 24 hours of a curative colon resection followed by 6 months of 5-FU/leucovorin is effective in prolonging the disease free interval and increasing survival in patients with Dukes' B3 or C colon cancer, when compared to patients who are treated with 5-FU/leucovorin only. Endpoints include: treatment failure--as defined by recurrence of local/regional or distant metastases--and survival.

Rev. 9/97 2.2 To determine if a week of perioperative continuous 5-FU affects disease-free survival and survival in patients with Dukes' B2 colon cancer.

2.3 To establish within ECOG a Central Tissue Repository for paraffin blocks and a frozen tissue bank.

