- All Dukes' B2, B3, and C patients must be re-registered  $\leq$  35 days post-op, after histopathological confirmation of tumor and Dukes' staging classification. Dukes' A, B1, and D patients will be removed from the study and will be treated at the discretion of their physician. Survival data will continue to be collected on Dukes' A, B1, and D patients until death.
- Rev. 9/97      Dukes' B2 patients will have perioperative 5-FU **continued** to completion, if so assigned, but will receive NO further adjuvant treatment.
- Rev. 9/97      Patients with Dukes' B3 and C disease must begin adjuvant 5-FU/leucovorin treatment between 21 and 35 days following surgery.
- 3.21      Must have pathologic classification of Dukes' B2, B3, or C disease (see Appendix IV for classification details) by the contributing institution.
- 3.22      Must be re-registered  $\leq$  35 days after surgery.
- 3.23      Have ECOG Performance Status of 0, 1 or 2.
- 3.24      Complete resection must have been performed with no evidence of residual disease or distant metastasis.
- 3.25      Distal margin of the tumor must not extend below the peritoneal reflection in the area of the rectum.
- 3.26      Single primary colon carcinoma without free perforation demonstrated. Patients with intestinal obstruction are eligible. Preliminary or complementary colostomy **does not** preclude entry of a patient.
- 3.27      Started perioperative 5-FU, if assigned, within 24 hours of surgery.

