#### 5.13 Pathologic Findings which Prevent Further Chemotherapy

Upon receipt of the final surgical pathology report from the contributing institution's pathology department, Dukes' A, B1, and D patients will have perioperative 5-FU **discontinued**, if so assigned, and will receive NO further adjuvant treatment. These patients will be treated at the discretion of their physician and survival data will continue to be collected on these patients until the time of death. Dukes' B2 patients will have perioperative 5-FU **continued** to completion, if so assigned, but will receive NO further adjuvant treatment. These patients will be followed on observation until relapse or death.

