### 5.62 Adjuvant 5-FU + Leucovorin

Rev. 9/97

Patients receiving adjuvant 5-FU/leucovorin continue the therapy for a total of 6 months or until recurrence. Once a patient has recurred according to the criteria in Section 6.1, he/she is considered off study and will be followed for survival.

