**9.0 STATISTICAL CONSIDERATIONS**

The primary objective of this study is to compare 6 months of adjuvant therapy with 5-FU and leucovorin to the same adjuvant therapy enhanced with perioperative therapy with continuous infusion 5-FU in Dukes' B3 and C patients with regard to the disease free interval and survival. This study is designed to be able to detect a clinically meaningful improvement in survival with 82% power while maintaining an overall significance level of 5% in a one-sided test, assuming patients are followed for 3 years after closure of the study to accrual. If 5 years of follow-up time were available, the power will be 91%. For Dukes' C patients, a clinically meaningful improvement in survival was taken to be an improvement in 5-year survival from 55% to 65%. For Dukes' B3 patients, this is an improvement in 5-year rates from 75% to 81%. To estimate the required sample sizes we assume exponential survival and a group sequential designed with an O'Brien-Fleming upper bound for early rejection of the null hypothesis of no treatment difference.

Assuming a 5-year survival rate of 75% for Dukes' B3 patients and 55% for Dukes' C patients in the adjuvant therapy alone arm, this study will require 800 analyzable patients (400 in each arm) to obtain the stated power using a stratified logrank test. Calculations assume that approximately 70% of the Dukes' B3 and C patients will be Dukes' C and 30% will be Dukes' B3. Since pathological staging is determined only after randomization, the accrual goal needs to be expressed in terms of Dukes' A,

B, C, and D patients. Using data on staging\* it is projected that 40% of all patients will be Dukes' B3 or C thus requiring a total accrual goal of 2000 patients to obtain the required number of B3 and C patients. As these projections are very approximate, accrual will be closely monitored during the first year and the accrual goals will be revised as necessary. For Dukes' A, B1, B2, and D patients, there will be no formal treatment comparisons. However, these patients will be followed to gather more information about disease progression and survival.

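### Sections 3.3 and 5.13 follow Dukes' B2 patients to relapse or death with no survival follow-up after relapse, in conflict with objective 2.2 and Section 9.0

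*Protocol*

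**What the plan says.** **B2 follow-up.** Section 3.3, on re-registration of patients randomized after surgery, states that "Dukes' B2 patients will be followed on observation until relapse or death". Section 5.13, which covers B2 patients whenever they were randomized, states: "These patients will be followed on observation until relapse or death". Section 3.2, on re-registration of patients randomized before surgery, has no such sentence. Its B2 text ends with perioperative 5-FU being completed, "if so assigned, but will receive NO further adjuvant treatment".

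**Other stages.** Sections 3.2 and 3.3 say: "Survival data will continue to be collected on Dukes' A, B1, and D patients until death". Sections 5.13 and 5.61 repeat this in substance. Under Section 5.62, a patient on adjuvant 5-FU/leucovorin (B3 or C) who recurs is "considered off study and will be followed for survival".

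**What the B2 data are for.** Objective 2.2 asks whether perioperative 5-FU "affects disease-free survival and survival in patients with Dukes' B2 colon cancer". Section 9.0 says: "For Dukes' A, B1, B2, and D patients, there will be no formal treatment comparisons". It adds that "these patients will be followed to gather more information about disease progression and survival".

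**The concern.** Sections 3 and 5 state a survival follow-up rule for every stage except B2. Section 5.13 puts the two rules in one paragraph: A, B1 and D to death, B2 to relapse or death. A site reading that paragraph could take the difference as intended and stop reporting on a B2 patient once relapse is recorded.

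Disease-free survival would not suffer, because relapse is already its event. Survival would. A patient whose follow-up ends at relapse is censored just when the risk of death rises, so the censoring is informative and a Kaplan-Meier estimate of B2 survival would be too high. If perioperative 5-FU changes the relapse rate, the arms would also be censored at different rates, and any survival effect that acts through relapse would largely drop out of the description that objective 2.2 calls for. The loss could also vary between sites, according to which section each one follows.

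**Working it through.** **1. The plan's own figures.** The only power figures in Section 9.0 are for the B3/C survival comparison: 82% with 3 years of follow-up after accrual and 91% with 5 years. They were reproduced to see whether B2 patients enter them.

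- Inputs (Section 9.0): 800 patients, 70% C and 30% B3; 5-year survival 55% against 65% (C) and 75% against 81% (B3); one-sided 5%; exponential survival; a final analysis at 6 years, 3 of them after closure to accrual. Uniform accrual over 3 years is assumed.
- Hazard ratios: C, ln(0.65)/ln(0.55) = 0.721; B3, ln(0.81)/ln(0.75) = 0.733. Event-weighted: 0.723.
- Chance of death for hazard λ, accrual A and further follow-up F: 1 − [exp(−λF) − exp(−λ(A+F))]/(λA). Summed over strata and arms, this gives about 253 deaths for F = 3 and 336 for F = 5.
- Power = Φ(√(d/4) × |ln HR| − 1.645). For d = 253: Φ(7.95 × 0.325 − 1.645) = 82.6%. For d = 336: 90.8%. Simulating the stated group sequential critical values gives 81.6% and 90.1%.

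The stated figures hold, and no B2 patient enters them.

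**2. The passages side by side.**

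| Place | Patients covered | After relapse |
|---|---|---|
| 3.3 | B2, randomized post-operatively | Observation runs to relapse or death; nothing further |
| 5.13 | All B2 | Same |
| 3.2 | B2, randomized pre-operatively | No follow-up rule |
| 3.2, 3.3, 5.13, 5.61 | A, B1, D | Survival data collected to death |
| 5.62 | Patients on adjuvant therapy (B3, C) | Survival follow-up stated |
| Objective 2.2 | B2 | Survival is an outcome |
| 9.0 | A, B1, B2, D | Followed for progression and survival |
| 7.1 calendar | B2, B3, C | Runs to year 5 and beyond; no stop at relapse |
| 11.0 follow-up form | Not limited by stage | Timed from study entry; no stop at relapse |
| Appendix VI follow-up form | EPP patients | Runs to death |

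Section 5.62 cannot fill the gap, because B2 patients receive no adjuvant 5-FU/leucovorin. What supports B2 survival follow-up after relapse is therefore 9.0, 7.1, 11.0 and Appendix VI. Sections 3.3 and 5.13 point the other way if read literally, and no passage says which governs.

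**3. Size.** Let f be the share of B2 deaths that follow a relapse, and g the share of those deaths that go unreported because the site stopped at relapse. The share of B2 deaths missed is f × g. The protocol gives neither. It also gives no B2 headcount: of the 2000 patients planned, 2000 − 800 = 1200 are A, B1, B2 or D together. As an assumption only, take f from 50% to 90%:

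- g = 1 (every such site stops at relapse): 50% to 90% of B2 deaths missed.
- g = 0 (every site follows the form schedule): none missed.

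This range shows what is at stake; it does not estimate the loss.

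**The case against.** The strongest objection is that the protocol does provide for B2 survival. Section 9.0 names B2 and says these patients are followed for survival. The calendar and form schedules, which tell sites what to do and send in, have no stop at relapse. Observation is also the name of the step to which B2 patients are re-registered, so 3.3 and 5.13 may only set how long that untreated step lasts, much as 5.62 sets how long adjuvant therapy lasts.

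Much of this stands. A reader might infer that B2 follow-up ends for good at relapse and that later deaths are not captured. The documents do not support that: neither sentence says that vital-status collection ends, and 9.0 says the opposite. Nor do they show a deliberate decision to forgo B2 survival.

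A reader might also infer from the gap in 3.2 that patients randomized before and after surgery are under different follow-up rules. That too goes too far, because 5.13 applies to both.

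The objection does not remove the conflict. Section 5.62 goes on to say what happens after recurrence, whereas 3.3 and 5.13 stop. The form schedule does not say that it overrides them.

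**Conclusion.** The point holds as an inconsistency in the current text. Sections 3.3 and 5.13 give a B2 follow-up rule that, applied literally, does not deliver the survival data asked for in objective 2.2 and Section 9.0, and it disagrees with the schedules in 7.1, 11.0 and Appendix VI. Deaths after relapse may go unreported at sites that apply it literally. How many cannot be computed from the protocol, and the range above rests wholly on assumed values.

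The consequence is limited to objective 2.2. The powered B3/C comparison is unaffected. Section 9.0 plans no formal B2 treatment comparison, so what is at risk is the B2 survival description and any informal look at the arms. It is still worth correcting, because objective 2.2 is a stated objective and vital status not collected at the time is hard to recover later.

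**What to change.** In Sections 3.3 and 5.13, state that B2 patients are observed until relapse and that survival data are then collected until death. Add the same sentence to Section 3.2. The three passages would then agree with objective 2.2 and Sections 9.0 and 11.0, and would match what 5.62 already says for patients on adjuvant therapy. The change concerns data collection only and does not touch treatment.

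The cost is one sentence in three places and continued vital-status follow-up of relapsed B2 patients. The form schedules already appear to cover that follow-up, and it is already required for the other stages.

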**For Dukes' B3 and C patients only:**

- Rev. 9/97, 8/99
- 3.35 Have WBC  $\geq 3000/\text{mm}^3$  and platelets  $\geq 100,000/\text{mm}^3$ ,  $\leq 1$  week prior to beginning adjuvant 5-FU/leucovorin therapy.
- 3.36 Have adequate renal (serum creatinine  $\leq 2.0$ ) and hepatic function (bilirubin  $\leq 2.0$ ), within one week prior to beginning chemotherapy.

**4.0 RANDOMIZATION/REGISTRATION PROCEDURES**

- Rev. 6/94, 3/95
- A signed HHS 310 Form, a copy of the institution's IRB-approved informed consent document, and written justification for any changes made to the informed consent for this protocol must be on file at the ECOG Coordinating Center before an ECOG institution may enter patients. The signed HHS 310, institution's informed consent, and investigator's justification for changes will be submitted to the following address:**
- Rev. 9/95

- Rev. 3/95, 9/95
- ECOG Coordinating Center  
Frontier Science  
ATTN: IRB  
[name]  
[name]  
[contact]
- Rev. 8/99

**Patients must not start protocol treatment prior to registration.**

Rev. 3/95, 7/96, 8/99

**NOTE: The submission of pathology material is required for ECOG patients and strongly encouraged for CALGB patients entered on this protocol (see Sections 7.2 and 10.0). Submission of tissue samples is not required for SWOG, ACOSOG, EPP or NSABP patients.**

Rev. 11/93

[name] assistant, [name], will be notified at time of perioperative randomization, and will then alert the Pathology Department of the institution in which the patient will undergo/has undergone the operation.

Rev. 7/96

**When randomizing ECOG or CALGB patients to E1292 (C9395), it is strongly recommended that they be simultaneously registered to laboratory companion protocol E3293.**

Rev. 3/95

Rev. 8/99

**For SWOG patients, the investigator will follow the instructions in Section 4.3.  
 For CALGB patients, the investigator will follow the instructions in Section 4.4.  
 For NSABP patients, the investigator will follow the instructions in Section 4.5.  
 For ACOSOG patients, the investigator will follow the instructions in Section 4.6.**

#### 4.1 ECOG Randomization

Rev. 9/95, 9/97

To randomize a patient, the investigator will telephone the Central Randomization Desk at the ECOG Coordinating Center at [contact]. For re-registration of Dukes' B2 patients to observation and Dukes' B3 or C patients to adjuvant 5-FU/leucovorin, see Section 4.2)

Rev. 9/95

The following information will be requested by the ECOG Coordinating Center:

##### 4.11 Protocol Number

##### 4.12 Investigator Identification

4.121 Institution name and/or affiliate

4.122 Investigator's name

##### 4.13 Patient Identification

4.131 Patient's name or initials and chart number

4.132 Patient's Social Security number

4.133 Patient Demographics

4.1331 Sex

4.1332 Birthdate (MM/YY)

4.1333 Race

4.1334 9 Digit Zip Code

4.1335 Method of Payment

#### 4.14 Eligibility Verification

Patients must meet all of the eligibility requirements listed in Section 3.1 OR 3.3. The randomization specialist will verify eligibility by asking questions from the STEP 1 eligibility checklist, which has been appended to the protocol. A confirmation of treatment assignment will be forwarded by the ECOG Coordinating Center.

Rev. 9/95

#### 4.2 ECOG Re-registration after Histopathological Staging

**NOTE: The contributing institution's pathology department must classify the colon cancer as Dukes' A, B1, B2, B3, C, or D within 2 weeks of the operation. Dukes' A, B1, and D patients will go off study; Dukes' B2, B3, and C patients must be re-registered as indicated below.**

Rev. 9/95

To register a patient, the investigator will telephone the Central Randomization Desk at the ECOG Coordinating Center at [contact]. The following information will be requested:

Rev. 9/95

#### 4.21 Protocol Number

#### 4.22 Investigator Identification

4.221 Institution name and/or affiliate

4.222 Investigator's name

#### 4.23 Patient Identification

4.231 Patient's name or initials and chart number

4.232 Patient's Social Security number

4.233 Patient Demographics

4.2331 Sex

4.2332 Birthdate (MM/YY)

4.2333 Race

4.2334 9 Digit Zip Code

4.2335 Method of Payment

#### 4.24 Eligibility Verification

Patients must meet all of the eligibility requirements listed in Section 3.2 OR 3.4. The randomization specialist will verify eligibility by asking questions from the STEP 2 eligibility checklist, which has been appended to the protocol. A confirmation of registration will be forwarded by the ECOG Coordinating Center.

Rev. 9/95

#### 4.3 SWOG Registration / Randomization

Investigators will call the Southwest Oncology Group Statistical Center at [contact] between the hours of 7:00 a.m. and 2:30 p.m. (PT) Monday through Friday excluding holidays. The Statistical Center will obtain and confirm all eligibility criteria and information as per Sections 4.1 and 4.2. In addition the Statistical Center will request the date informed consent was obtained and the date of IRB approval for each entry. The Statistical Center will then contact the ECOG Coordinating Center to register and randomize the patient after which the Statistical Center will contact the Institution to confirm registration and relay the treatment assignment for that patient. The ECOG Coordinating Center will forward a confirmation of treatment assignment to the Statistical Center for routing to the participating Institution.

Rev. 9/95

Rev. 9/95

#### 4.4 CALGB Registration/Randomization

CALGB randomization will be accepted through the Main Institution only, prior to initiation of therapy. Confirm all selection criteria listed in Section 3.0. Call the CALGB Data Management Center [contact], Monday to Friday, 9:00 a.m. to 5:00 p.m. Eastern Time). The CALGB Registration Desk will then contact the ECOG Coordinating Center to register and randomize the patient, after which the CALGB office will contact the Institution to confirm registration and relay the treatment assignment for that patient. The ECOG Coordinating Center will forward a confirmation of treatment assignment to the CALGB Office for routing to the participating Institution.

Rev. 9/95

Rev. 9/95

Rev. 3/95,8/99

#### 4.5 NSABP Registration/Randomization

**Note: A signed 310 form, indicating current IRB approval for the study, must be on file at the NSABP Biostatistical Center before any NSABP institution may enter a patient.**

NSABP Institution Investigators or Data Coordinators must fax a completed Eligibility Checklist and a signed, dated, and witnessed Consent Form to the NSABP Biostatistical Center at [contact] between the hours of 8:30 a.m. and 4:00 p.m. (eastern time) Monday through Friday excluding holidays. Senders must include a telephone number/fax number on the cover sheet so they may be contacted after the NSABP receives the randomization information from ECOG. The randomization specialist at the NSABP Biostatistical Center will confirm the eligibility and patient selection criteria and will then contact the ECOG Coordinating Center to register and randomize the patient. The NSABP randomization specialist will then contact the institution to confirm registration and relay the treatment assignment for that patient. The ECOG Coordinating Center will forward a confirmation of treatment assignment to the NSABP Biostatistical Center for routing to the participating institution. The entire randomization procedure must be completed in time for the patient to begin therapy no later than 24 hours after surgery; therefore, it is important that an institution Investigator or Data Coordinator fax the necessary information to the NSABP Biostatistical Center as soon as possible after the patient's surgery, when randomizing post-operatively.

Rev. 8/99

#### 4.6 ACOSOG Registration/Randomization

A signed HHS 310 Form, a copy of the institution's IRB-approved informed consent document, and written justification for any changes made to the informed consent for this protocol must be on file at the ACOSOG Coordinating Center before an ACOSOG institution may enter patients (see SOP:IRB). These will be submitted to:

American College of Surgeons Oncology Group  
ATTN: [name]  
[name]  
[name]  
[contact]  
[contact]  
E-mail: [contact]

The IRB approval date and Form 1572 date must be within one year of patient entry into the study. Patients must not start protocol treatment prior to registration. Treatment should start within three working days of registration.

To register eligible patients on study, the registering site will access the ACOSOG web page at <http://www.acosog.org>.

The site will be asked for the following information: Study Number registering for (E1292), institution identifier, and investigator identifier. All of the above information are required for the registration process to continue. Once the above information have been verified, further registration instructions will be provided to the registering site to complete the registration process and get the randomization assignment. The registration process can likely be completed in 15 minutes or less under normal circumstances.

Rev. 8/99

